### Power Calculations

Sample size estimations were performed using G*Power 3.1. Sample size estimations were performed for all analyses, and the final targeted sample size was selected so that the analysis requiring the largest number of participants could be adequately powered.

As our proposed treatment is new and the goal of this project is to collect initial data on its effectiveness, formal power analysis cannot be conducted. However, based on the literature on the effectiveness of specialized ED care [13-15,99-104], we expect a medium effect size (f^2^=0.15). Recent work in adult patients in a specialized tertiary care ED program also showed that fully web-based care and fully in-person outpatient care both yielded a similar medium effect size [105]. Thus, we expect our hybrid model to yield medium effect sizes. This implies that the sample size required to reach a level of significance of P=.05 with a power of 0.80 is 68 participants. By testing three moderators and with an assumed dropout rate of 25% [17,42,43], we would need to recruit 98 people to test our hypotheses. Therefore, a total of 100 patients will be recruited.

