### Objectives and Hypotheses

The primary objective of this study is to describe the feasibility and acceptability of flexible, modular, and hybrid IACP for adolescents with EDs. Secondary aims include describing the baseline characteristics of the adolescents who enroll in the IACP, describing the preliminary effectiveness of the IACP for adolescents with EDs in an uncontrolled naturalistic setting, and describing the moderating role of age, ED diagnosis (eg, anorexia nervosa vs other ED diagnoses), length of illness, and level of attendance on clinical response to the IACP.

We hypothesize that recruiting and retaining participants in the IACP would be feasible and acceptable. We expect that participants will mostly present restrictive ED symptomatology, which is representative of the patient population seen in the ED clinic where the study will be conducted; participants will present comorbid symptomatology and ED-related behaviors, such as anxiety and depressive symptoms [31,32], high levels of affective reactivity [33] and perfectionism scores [34], poor coping [35] and self-esteem [36] skills, and high levels of social media use [37], as reported in the literature. We expect that participation in the IACP will be associated with a reduction in ED psychopathology, from baseline to the end of treatment, and that patient age, ED diagnosis, length of illness, family connectedness, and the number of hours of therapy attended will act as moderators of the preliminary effectiveness of the intervention. Although there is no consensus on moderators of treatment outcomes in the adolescent population, these moderators were chosen based on limited evidence from several reviews [8,38,39] that have identified individual, clinical, and family-related factors that are related to treatment response.

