Adherence to protocol	At least 70% (70/100) of participants complete at least one therapeutic session per week of treatment in the IACP. At least 70% (70/100) of participants complete all pre- and postintervention questionnaires. At least 70% (70/100) of participants complete at least one therapeutic session per week and all pre- and postintervention questionnaires.

^a^IACP: Intensive Ambulatory Care Program.

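### The sample size is worked out for three moderators and 25% dropout, but five moderators are planned and the effectiveness analysis set is narrower, so the claim of adequate power holds only under an unstated choice of test

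*Protocol article*

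**What the plan says.** The Power Calculations section sets its own rule: "the final targeted sample size was selected so that the analysis requiring the largest number of participants could be adequately powered". It takes a medium effect ("we expect a medium effect size (f^2^=0.15") and concludes that "the sample size required to reach a level of significance of P=.05 with a power of 0.80 is 68 participants". It then adds moderators and attrition: "By testing three moderators and with an assumed dropout rate of 25% [17,42,43], we would need to recruit 98 people to test our hypotheses". The target is rounded up: "Therefore, a total of 100 patients will be recruited". The same section says that a formal power analysis is not possible for a new treatment. It names no test, number of tested predictors or multiplicity adjustment.

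The number of moderators differs between sections:
- **Power Calculations:** three, not named.
- **Objectives and Hypotheses, secondary aim:** four (age, diagnosis, length of illness, attendance).
- **Objectives and Hypotheses, hypotheses:** five. The text expects that "patient age, ED diagnosis, length of illness, family connectedness, and the number of hours of therapy attended will act as moderators".
- **Statistical Analysis:** the same five, with attendance in place of hours attended.

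Attrition and Compliance limits the preliminary-effectiveness analysis to participants who attend at least weekly and also complete both sets of materials. Table 1, under Data Collection, gives the target for that combination: "At least 70% (70/100) of participants complete at least one therapeutic session per week and all pre- and postintervention questionnaires".

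**The concern.** The section promises a sample size set by its most demanding analysis, yet the calculation covers fewer moderators than the plan tests. It also deducts a loss (25%) smaller than the one implied by the target for the analysis set (30%). If several moderators are tested with error control, or tested jointly, the study has less than the stated 0.80. A null moderator result could then be reported as adequately powered when it was not. A reader also cannot tell which test lies behind 68 or 98, and so cannot judge whether the claim survives five moderators.

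**Working it through.** **Inputs.** From Power Calculations: f² = 0.15, alpha 0.05, power 0.80, three moderators, 25% dropout, 100 recruited. From the hypotheses and Statistical Analysis: five moderators. From Attrition and Compliance with Table 1: 70 of 100 in the effectiveness set.

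**Method.** Power of the F test in fixed-model linear regression. The noncentrality is λ = f² × N. The degrees of freedom are u (predictors tested) and N − p − 1 (p predictors in the model). Number to recruit = analysed N / (1 − loss), rounded up. The plan uses mixed models; with two time points and complete pairs I treat moderation of change as a regression of change on the moderators.

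**Step 1: the plan's 68.** Joint F test of two predictors at 0.05: N = 67 gives power 0.798 and N = 68 gives 0.804. So 68 is reproduced exactly. One predictor would need 55 and three would need 77.

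**Step 2: the plan's 98.** Single-df tests of three moderators, each at 0.05/3 = 0.0167: N = 72 gives 0.795 and N = 73 gives 0.801. Then 73 / 0.75 = 97.3, so 98. This uses exactly the stated three moderators and 25% dropout.

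**Step 3: do the two figures belong together?** 68 / 0.75 = 90.7, so 68 alone inflates to 91, not 98. The 68 fits a 2-df test at 0.05, and the 98 fits 1-df tests at 0.0167. Both set-ups are my inference.

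**Step 4: five moderators, on the reading that gives 98.** Single-df tests at 0.05/5 = 0.01 need 82 analysed. 82 / 0.75 = 109.3, so 110 recruited. For the four in the secondary aim (0.0125), 78 are needed, and 78 / 0.75 = 104.

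**Step 5: power with 100 recruited, f² = 0.15.**

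| Test | 75 analysed | 70 analysed |
|---|---|---|
| Three moderators, 1 df each at 0.05/3 | 0.81 | 0.78 |
| Five moderators, 1 df each at 0.05/5 | 0.76 | 0.72 |
| Five moderators, one joint 5-df test at 0.05 | 0.70 | 0.66 |
| Any one moderator, 1 df at unadjusted 0.05 | 0.91 | 0.89 |

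The joint 5-df test needs 92 analysed, and 92 / 0.75 = 122.7, so 123 recruited. For the unadjusted row, the chance of at least one false positive in five independent tests is 1 − 0.95⁵ = 0.23.

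**The case against.** The strongest defence is that the plan's figure is sound for what it says it covers. 98 comes out exactly for three moderators with 25% dropout, and 75 completers then have power 0.81. That stands. A reader might infer that 98 is an arithmetic error and that 103 is the right value, because a joint test of three predictors needs 77 and 77 / 0.75 = 102.7. The document does not support this. It never names a joint test, and one unstated reading that misses 98 cannot prove it wrong when another reaches it.

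A second defence is that the Statistical Analysis section does not prescribe a joint test or an adjustment. If each moderator is tested alone at 0.05, power stays near 0.9 for five as for three. That also stands, so it would be too strong to say without condition that 0.80 is not delivered. But on that reading only 55 analysed participants are needed, which explains neither 68 nor 98, and error across the five tests is uncontrolled.

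Third, 70 of 100 is a feasibility floor, not a forecast. That is fair, and more may qualify. Still, the 25% allowance is for dropout alone, while the analysis set also requires weekly attendance and complete questionnaires. A study that just meets its own target analyses 70.

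Finally, the section itself disclaims formal power analysis, and moderation is a secondary, descriptively worded aim. This lowers the severity. It does not reconcile the disclaimer with the claim of adequate power in the preceding paragraph.

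**Conclusion.** The point holds as a mismatch between sections, not as an arithmetic error. The calculation covers three moderators, and the hypotheses and analysis test five. The loss deducted leaves 75, and the target for the effectiveness set is 70. On the reading that reproduces 98, power for each of five moderators is about 0.76 with 75 analysed and 0.72 with 70. Even three moderators reach only about 0.78 with 70. A joint test of five gives 0.70 and 0.66. For five moderators, the claim that the most demanding analysis is adequately powered therefore holds only if they are tested singly without adjustment.

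These figures rest on f² = 0.15 applying to each moderator (or to the five together in the joint test) and on the regression approximation above. The Bonferroni set-up behind 98 is inferred from the match, not stated. The severity is moderate: the primary objective is feasibility and acceptability, and this finding does not affect it.

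**What to change.** Keep 100 recruited and revise the text:
1. Use one moderator list in the secondary aim, the hypotheses, Power Calculations and Statistical Analysis, with one definition of attendance.
2. Name the test, the number of tested predictors and the alpha behind 68 and behind 98.
3. Restate power under the named test at the analysed number: 70, or 75 if the analysis set is widened to all completers. For five moderators at 0.05/5 that is 0.72 or 0.76. Alternatively, name three powered moderators in advance and label the others exploratory, giving 0.78 or 0.81 at 0.05/3.
4. Withdraw or qualify the sentence on adequate power, and reconcile it with the statement that no formal power analysis is possible.

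The cost is one rewritten paragraph and matching edits to the moderator lists, with no added participants. Unless unadjusted single tests are named, the stated power for five moderators will be less favourable than 0.80.

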### Statistical Analysis

Statistical analyses will be performed using SPSS version 27.0. Feasibility and acceptability will be analyzed by summarizing quantitative data from (1) clinician-reported recruitment rate, retention rate, and adherence to protocol using descriptive statistics; (2) weekly satisfaction surveys of individual and group activities; and (3) postintervention surveys of overall satisfaction and satisfaction with the web-based mode of intervention. Qualitative data from both the weekly and overall satisfaction surveys will be analyzed using conventional content analysis. Patient characteristics at baseline will be summarized using descriptive statistics.

The preliminary effectiveness of the IACP intervention will be examined using general linear mixed models, with changes in global EDE-A scores from baseline to the end of treatment as the primary outcome. Appropriate covariates (eg, number of attended sessions) and random factors (eg, therapist) may be added to the statistical model for exploratory analysis. Similar general linear mixed model analyses will be run for the secondary outcome measures (Table 3), comparing scores from the baseline to the end of treatment. Finally, general linear mixed models will also be used to study the moderating role of the level of attendance and other clinical and psychosocial factors such as age, length of illness, ED diagnosis (anorexia nervosa vs other types of ED), and family connectedness on the primary outcome (change in EDE-A scores from baseline to end of treatment).

### Ethics Approval and Participant Safety

The Scientific Committee of the Sainte-Justine University Hospital Center Ethics Committee (FWA00021692), which was designated by the Quebec government (Ministère de la Santé et des Services Sociaux du Quebec) in Montreal, reviewed and approved the study protocol (project ID number: 2022-3925). Concerning the intervention itself, the risks involved are minimal and inherent to participating in therapy, such as being confronted with difficult information regarding one’s own mental health, behaviors, attitudes, etc, which can lead to stress or anxiety. However, this is a part of the treatment process and is expected to lead to positive therapeutic outcomes. The risks related to the evaluation of the intervention are minimal. There will be no inconveniences in terms of travel time and time spent responding to questionnaires other than that required for the participants’ normal follow-up in the IACP. If participants disclose worrisome information in the questionnaires, especially those related to suicidal ideation, the clinical program coordinator (a clinical psychologist) will contact them promptly to provide appropriate support. The clinical program coordinator will refer the participants to the necessary services to ensure their safety. The participants will be notified in advance that the clinical program coordinator may disclose this information to their parents or caregivers. Risks related to data and information-sharing with the research team as well as the measures in place to maintain participant confidentiality (deidentification of all data, transfer of data via a secure email account, and data storage on secure hospital servers) will also be discussed with all participants and parents during the intake meeting with the clinical coordinator.

## Results

Recruitment for the study and data collection will be conducted on a rolling basis from winter 2022 to fall 2023. The data analysis and manuscript writing are expected to be completed by the summer of 2024.

## Discussion

### Anticipated Outcomes

We anticipate that our study will demonstrate the feasibility of running an innovative hybrid (web-based and in-person) IACP for adolescents in a specialized ED clinic located in a tertiary care hospital in a large urban center. We also anticipate that the intervention will be acceptable to both participants and their parents. We anticipate that the intervention will lead to a reduction in ED psychopathology, and that greater levels of participation in the IACP will be associated with a greater reduction in symptoms. We anticipate that participants recruited to participate in the study will represent a subset of the youth population with EDs on the more severe end of the disease spectrum (as patients with less severe illnesses would be less likely to be referred to the specialized ED program by their treating physician). Therefore, we anticipate that most study participants will present with severe ED symptoms (as measured by the EDE-A), comorbid symptoms of anxiety and depression, and personality traits predisposing them to perfectionism and low self-esteem, as reported in the literature [106,107].

### Future Implications

The IACP could represent a novel mode of treatment in terms of content, therapeutic approach, and mode of delivery, and would present important advantages for accessibility and patient-centered care, given its flexible and hybrid (in-person and web-based) nature. Indeed, the intent is to make the program as accessible as possible by removing barriers such as geographic distance and interference with school and family functioning.

If the results of this study show that such an approach is feasible, acceptable, and preliminarily effective, the model can be easily applied at other sites or in a larger population for a few reasons. First, the initial and final assessments used standardized questionnaires with favorable psychometric properties in child and adolescent populations. Second, guidelines for individualized treatment module selection will be created, allowing clinical coordinators to use predefined threshold scores from baseline assessments to elaborate treatment plans. Similarly, guidelines for evaluating whether participants should participate in regular or extended programs will be created.

### Strengths and Limitations

Our study protocol has several strengths. First, the outcome measures will be completely integrated into regular clinical evaluations of patients participating in the IACP. As such, participants and their families will not be required to spend any additional time participating in the study. Second, the novel hybrid model of treatment will facilitate the incorporation of sessions into families’ schedules and is flexible and adaptable to individuals’ living situations, favoring both participation in the IACP and study completion. Third, the treatment program will be individualized and tailored to each participant’s needs. This will ensure that participants receive treatment that focuses on the most pressing issues related to their ED. Given the alignment of treatment modules and standardized pre- and postintervention questionnaires, data analysis is likely to capture the most salient changes in symptomatology. Fourth, building on expanding literature, a comprehensive battery of questionnaires and outcomes will allow for meaningful analyses of several contributing factors related to the treatment of EDs in adolescents by making optimal use of several validated questionnaires. Finally, participants with a broad range of ED diagnoses will be included to appropriately represent diverse symptom presentations.

This study has a few limitations. First, being a single-site study, recruitment will be limited to the number of patients receiving care at the study site, which may limit the final sample size and generalizability of our findings. However, it should be noted that the study will be conducted in the largest tertiary pediatric care hospital in Quebec, a Canadian province with a population of 8.5 million inhabitants. Therefore, the results of this study can be generalized to other sites in large North American urban centers. Second, the naturalistic trial design and individualized treatment approach will make it so that some of the analyses and conclusions may be impacted by external confounders (such as changes in primary treatment, seasonality, and external stressors). However, it will allow for a better understanding of the real-world feasibility and acceptability of this type of day treatment program for EDs in adolescents. Third, given the highly flexible and personalized nature of the IACP, it will not be possible to compare the feasibility and preliminary effectiveness of in-person vs web-based treatment modules. However, acceptability data (satisfaction questionnaires) may provide important clues to the participants’ appreciation of the in-person and web-based components of the program. Finally, the short duration of follow-up in this project will not allow for long-term assessment of the effectiveness of treatment in reducing ED symptomatology. Future work may include long-term follow-up of youth participating in the IACP, as well as more detailed analyses on the effectiveness of different components of the program (eg, in-person vs web-based modules).

### Conclusions

Given the high incidence of EDs in the adolescent population and the important physical, psychological, and social impacts of these illnesses, research on scalable and adaptable treatment programs is crucial. Evaluating the feasibility, acceptability, and effectiveness of intensive ambulatory treatment delivered in a hybrid model is in line with this objective. Furthermore, the intervention we describe, using a hybrid and family-focused modular approach that adapts treatment to individual participants, has seldom been described in the existing literature. Despite its limitations, the findings of this study will help evaluate and refine our hybrid (in-person and web-based) IACP in real-life practice. It will also allow us to gain a better understanding of which patients could benefit from it the most. It is our hope that our study may help inform and improve the care of patients with EDs, both in our center and in other centers worldwide.

## Appendix

Multimedia Appendix 1 Secondary outcome measures assessing comorbidities and eating disorder associated behaviors.

## Abbreviations

DSM-5: Diagnostic and Statistical Manual of Mental Disorders, Fifth Edition
ED: eating disorder
EDE-A: Eating Disorder Examination Questionnaire Adolescent version
EDE-Q: Eating Disorder Examination Questionnaire
IACP: Intensive Ambulatory Care Program
